##### Qualitative Assessments: Usability

Participants will perform think-aloud sessions throughout the user testing to share how each prototype has been able to capture their preferences for treatment outcomes or whether the display of preferences is useful. We will engage participants as co-designers, soliciting feedback on the available functions in the current prototypes and encouraging them to make suggested improvements to the design of the EHT as well as the visualization depicting user preferences. Information obtained during user testing will be aggregated per group and used for iterative improvements to the prototype. Each group will evaluate prototypes that have been revised based on stakeholder feedback from the previous groups.

##### Qualitative Assessments: Semistructured Interviews

Semistructured interviews will be conducted to elicit feedback from participants on whether they understood various aspects of the tool, including but not limited to (1) definitions of the attributes, (2) ability to distinguish between the levels of attributes as presented, (3) which choice task series (BWS or DCE) was preferrable, and (4) whether they feel patients and family caregivers would utilize this tool. Data will be collected through the recording of interviews.

##### Participant Characteristics: Additional Validated Measures

Additional validated assessment measures will be included in the study to assess whether various attributes are correlated with treatment decisions (Multimedia Appendix 2). Participants will be assessed on memory skills, as well as on their electronic health literacy skills.

##### Participant Characteristics: Memory Skills

Participants will be asked to repeat a series of numbers during both the forward and backward assessments of the Digit Span test, a subset of the Wechsler Intelligence Scale, which when used separately, are considered validated measures of working memory [51,52]. Participants will be assessed on their ability to repeat strings of numbers, increasing in length by 1, until an error occurs on the reiteration of the string, or they reach a string length equal to 9. Participants will run through all forward strings before moving to the digit span backward test, in which they will be asked to repeat strings of numbers in reverse order. While the digit span test can be conducted by a verbal facilitator using only pencil and paper, we have chosen to use the computerized version, as there are benefits to the accessibility of both participants with hearing abilities and participants with hearing impairment, and elimination of verbal discrepancies (ie, rate or clarity of speech) that may exist among facilitators [53]. The computerized version of the digit span test is an appropriate measure to assess the working memory of users performing tasks on each prototype.

##### Participant Characteristics: Health Literacy

The eHealth Literacy Scale (eHEALS) and the eHealth Literacy Scale for Carers (eHEALS-Carer) are validated measures to assess the skills in acquiring health information through the use of technology, for oneself or the care of others, respectively [54]. The eHEALS assessment was developed to measure 6 skills: traditional literacy, health literacy, information literacy, scientific literacy, media literacy, and computer literacy [55]. The eHEALS model was further adapted to validate these same literacies among primary caregivers [56]. Each assessment consists of 8 questions, each measured on a 5-point Likert scale, ranging from “strongly agree” to “strongly disagree.” A score upon completion can range from 8 to 40, with higher scores representing higher eHealth literacy [57]. The eHEALS and eHEALS-Carer assessments are appropriate measures to evaluate the health literacy of users performing tasks on each prototype and will allow us to determine whether variability exists between participant types.

All in-person assessments and subjective measures have been converted to electronic surveys, and the data collected will be entered directly into REDCap. Paper assessments will be made available for participants who prefer this method, in which case all responses will then be manually transferred from the paper assessment to REDCap by a member of the study team.

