#### Phase 3: Evaluation With Patients, Caregivers, and Health Care Workers

##### Overview

Participants will be asked to complete a baseline questionnaire online via REDCap before the user testing session. Questions related to the following domains will be asked of patients: race, ethnicity, education, household income, marital status, living situation, employment, technology comfort level, and insurance. Questions related to the following domains will be asked of caregivers: race, ethnicity, education, household income, marital status, living situation, employment, technology comfort level, insurance, length of time as a caregiver, and relationship to the patient. Health care workers will complete a short demographic questionnaire related to their role, their time in this role, and their exposure to patients with AML.

Further, patients will be asked to self-report on 2 of the 3 Simplified Geriatric Assessment (sGA) measures, which include the activities of daily living and the instrumental activities of daily living (Multimedia Appendix 2). The sGA tool was selected for reliability, brevity, and prognostic value in classifying the fitness level of older adults. Study coordinators will work with physicians to help participants complete the Cumulative Illness Rating Scale-Geriatric (CIRS-G), an assessment of comorbidity for enrolled patients [58]. Results from the activities of daily living, instrumental activities of daily living, CIRS-G, along with patient’s ages, will be calculated and used to classify patients as either fit, unfit, or frail [59].

If participants are unable to complete the self-reported preassessments online, they will be administered by study personnel either in person or over the phone.

Patient-caregiver pairs will be divided into 2 groups, each consisting of 10 patients and 10 caregivers. Patients and caregivers will be asked to participate in think-aloud sessions and semistructured interviews providing evidence on the usability of both the DCE and BWS within the prototypes, whether they understood various aspects of the tool, and whether they feel patients and family caregivers would utilize this tool. In addition to the assessments listed below, patients and caregivers will be involved in the same quantitative and qualitative assessments described in phase 2.

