##### Participant Characteristics

Patients and caregivers will complete the additional assessments (memory skills and health literacy) as described in phase 2. Patients will also take an additional assessment of cognition levels, as described below.

The Blessed Orientation Memory Concentration (BOMC) assessment is a validated measure of cognitive function. This assessment will be conducted through verbal facilitation by a study team member, in which patients will be asked to repeat and recall information, replicating their memory and concentration skills [62]. The final score is based on a weighted calculation and assesses the likelihood of cognitive disability, with a higher score representative of a clinically meaningful cognitive impairment [63]. The BOMC assessment tool is an appropriate measure to evaluate the memory and concentration of users performing tasks in each prototype.

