#### Quantitative

The paired *t* test will be utilized to evaluate the statistical significance of the PSSUQ, SEQ, NASA-TLX, and performance (time taken for task completion and the number of errors committed) of participants using both the DCE and BWS within the prototypes for each group in all relevant phases. Analysis of variance tests will be utilized to evaluate whether statistical differences in the DCE and BWS occur across groups for these same measures. We will consider *P* values of less than .05 to have statistical significance, and 95% CIs will be used to establish differences between the DCE and BWS both within and across groups.

We aim to use the data from preassessments (demographics, geriatric assessment), in-person assessments (cognition, memory, and health literacy), digit span, and health records to determine predictor variables with patient treatment preferences, and to determine whether health literacy variance exists between patients and caregivers. Analysis of preassessments will include basic statistics (eg, mean, SD, and range).

All analysis will be performed in SAS JMP Pro (SAS Institute) for summarizing and grouping study results both between and across groups. We will work with an experienced statistician to ensure that we utilize appropriate methods and theories for data analysis.

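### If caregivers complete only the eHEALS-Carer, the planned patient-caregiver comparison of health literacy cannot be separated from the change of scale (minor, secondary point)

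*Protocol article*

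**What the plan says.** The subsection Participant Characteristics: Health Literacy (phase 2) names two instruments. It describes them as measuring skill in obtaining health information through technology "for oneself or the care of others, respectively". On how the two relate, it says: "The eHEALS model was further adapted to validate these same literacies among primary caregivers". The format is common to both: "Each assessment consists of 8 questions, each measured on a 5-point Likert scale", and "A score upon completion can range from 8 to 40, with higher scores representing higher eHealth literacy". It then states that the two instruments "will allow us to determine whether variability exists between participant types".

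The Quantitative subsection of Data Analysis repeats this as an aim for two named types: "to determine whether health literacy variance exists between patients and caregivers". That paragraph names no test for the contrast.

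Phase 3 carries the measures forward: "Patients and caregivers will complete the additional assessments (memory skills and health literacy) as described in phase 2". Phase 4 refers back to phase 3 in the same way. On numbers, the phase 3 Overview says: "Patient-caregiver pairs will be divided into 2 groups, each consisting of 10 patients and 10 caregivers".

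The article does not say which participant type completes which scale. It points to Multimedia Appendix 2 for the assessments, and that appendix is not among the documents at hand.

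**The concern.** The article asserts that these instruments support a comparison between participant types. On the natural reading, patients answer about managing their own health and caregivers answer about looking after someone else. The instrument then changes exactly where the participant type changes.

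The change of referent could move scores either way. A caregiver may feel confident finding information for personal use and less so for another person's blood cancer, or the reverse. A shift between versions could therefore create an apparent gap between patients and caregivers or hide a real one. At stake is one stated secondary conclusion, whether the two types differ in health literacy.

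**Working it through.** **1. The article's own figure.** Eight items scored 1 to 5 give a minimum of 8 × 1 = 8 and a maximum of 8 × 5 = 40. The stated range of 8 to 40 is reproduced for each version.

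**2. What the contrast estimates.** If each type completes only its own version,

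expected mean difference = (true literacy difference) + (version difference).

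The data supply one contrast and there are two unknowns, so the terms cannot be estimated separately. This holds whatever the sample size and whatever the test. A common range does not remove the second term: two scales can both run from 8 to 40 and still give different averages for people of equal literacy. The article mentions no equating, no conversion between the versions and no instrument given to both types.

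**3. How much a shift could matter (illustration only).**

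Inputs from the article:
- Pairs in phase 3: 2 groups × 10 = 20.
- Significance level: .05. It is stated for the DCE-BWS comparisons and borrowed here; two-sided is assumed.

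Assumed inputs, because the article gives none:
- True literacy equal in patients and caregivers.
- Version shift of 2 points, that is 8 items × 0.25 point.
- SD of the within-pair difference of 5, 6 or 8 points.
- A paired t test.

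The noncentrality is shift ÷ (SD ÷ √n), with 19 degrees of freedom and critical value 2.093:

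| SD of difference | Noncentrality | Probability of P<.05 |
|---|---|---|
| 5 | 2 ÷ (5/√20) = 1.789 | 0.397 |
| 6 | 2 ÷ (6/√20) = 1.491 | 0.294 |
| 8 | 2 ÷ (8/√20) = 1.118 | 0.186 |

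With no shift the figure is 5%. The same formula at an SD of 6 gives about 11% for a 1-point shift and 56% for a 3-point shift.

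**4. Sensitivity to the test.** An independent-samples t test with 20 per type and a per-person SD of 6 gives 8%, 18%, 34% and 54% for shifts of 1, 2, 3 and 4 points. At a 2-point shift it gives 34% with a per-person SD of 4 and 12% with 8. These SDs are per person, not of the difference, so they should not be set line by line against the table.

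**The case against.** The strongest objection is that the allocation of scales is inferred. The article ties each scale to a referent, not to a participant type, and phase 3 says only that patients and caregivers complete the health literacy assessment already described, a description that names both scales. Caregivers completing both would fit the text, and the missing appendix may settle it. This stands, and the point is therefore conditional.

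Second, the carer version is presented as an adaptation covering the same literacies, in an identical format, and the cited validation work may support comparability. This is fair as far as it goes: the shift may be small. But validity of each scale in its own population is not equivalence of scores between scales, and the article claims the comparison without a caveat.

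Third, the illustration rests on an assumed shift, assumed SDs and an assumed test. This also stands. The rejection probabilities show sensitivity and do not estimate a bias.

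Three stronger readings are tempting but not supported:
- A reader might infer that the plan uses an inefficient unpaired test on paired people. No test is named for this contrast; the paired t test and analysis of variance are assigned to the usability, workload and performance measures.
- A reader might infer that a material bias has been shown. Nothing in the document gives the size or direction of a shift.
- A reader might infer that the health literacy data are useless or that the main results suffer. Each type's score in its own role can still be described. The study calls itself primarily descriptive, and its DCE-BWS comparisons are made within participants.

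**Conclusion.** The point holds in a conditional and minor form. If caregivers complete only the eHEALS-Carer, a patient-caregiver difference in health literacy, or its absence, cannot be attributed to literacy rather than to the change of referent. That conclusion follows from the design and needs no assumed figure.

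The practical size is unknown. Under the assumptions set out above (20 pairs, a 2-point shift, SD of the difference 5 to 8, paired t test, equal true literacy), a spurious significant result would occur in about 19% to 40% of studies, against the nominal 5%. If Multimedia Appendix 2 shows that caregivers also complete the eHEALS, the confounding disappears for that score and only a clarifying sentence is needed. The contrast is secondary, and the usability, workload and performance comparisons of the two prototypes do not depend on it.

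**What to change.** State which participant type completes which scale. If caregivers do not already complete the eHEALS, add it for them, answered about themselves. Base the patient-caregiver comparison on that common 8-item scale, by patient-caregiver pair, and keep the eHEALS-Carer as a descriptive caregiver variable.

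Phase 3 recruitment began in January 2022, so some caregivers may already have been tested. For any tested without the eHEALS, report each scale separately and draw no conclusion about a difference between types.

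The cost is eight more items per caregiver in REDCap, where the assessments are already electronic, plus a sentence or two in the analysis section. The added respondent burden is the only real downside.

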#### Phase 3: Evaluation With Patients, Caregivers, and Health Care Workers

##### Overview

Participants will be asked to complete a baseline questionnaire online via REDCap before the user testing session. Questions related to the following domains will be asked of patients: race, ethnicity, education, household income, marital status, living situation, employment, technology comfort level, and insurance. Questions related to the following domains will be asked of caregivers: race, ethnicity, education, household income, marital status, living situation, employment, technology comfort level, insurance, length of time as a caregiver, and relationship to the patient. Health care workers will complete a short demographic questionnaire related to their role, their time in this role, and their exposure to patients with AML.

Further, patients will be asked to self-report on 2 of the 3 Simplified Geriatric Assessment (sGA) measures, which include the activities of daily living and the instrumental activities of daily living (Multimedia Appendix 2). The sGA tool was selected for reliability, brevity, and prognostic value in classifying the fitness level of older adults. Study coordinators will work with physicians to help participants complete the Cumulative Illness Rating Scale-Geriatric (CIRS-G), an assessment of comorbidity for enrolled patients [58]. Results from the activities of daily living, instrumental activities of daily living, CIRS-G, along with patient’s ages, will be calculated and used to classify patients as either fit, unfit, or frail [59].

If participants are unable to complete the self-reported preassessments online, they will be administered by study personnel either in person or over the phone.

Patient-caregiver pairs will be divided into 2 groups, each consisting of 10 patients and 10 caregivers. Patients and caregivers will be asked to participate in think-aloud sessions and semistructured interviews providing evidence on the usability of both the DCE and BWS within the prototypes, whether they understood various aspects of the tool, and whether they feel patients and family caregivers would utilize this tool. In addition to the assessments listed below, patients and caregivers will be involved in the same quantitative and qualitative assessments described in phase 2.

Health care workers will be divided into 2 groups, each consisting of up to 5 users. Health care workers will participate in qualitative assessments as described in phase 2 to assess the general usability of both the DCE and BWS within the prototypes and whether they would find this tool beneficial and would recommend its use for patients and caregivers.

Following recommendations from Francis et al [60], we have established sampling sizes within each group (up to 20 patient-caregiver pairs and 5 health care workers), a stopping criterion (set at 3 interviews), and the number of additional interviews we will conduct, to demonstrate that all themes have been introduced.

##### Qualitative Assessments: Cognitive Workload

Cognitive task analysis will be performed to gain insight into the thought processes and mental strategies of patients as they work through each prototype [61]. After completion of the task, a member of the study team will ask the participant to walk them through their process for selecting each treatment preference. Data will be collected through the recording of interviews.

##### Participant Characteristics

Patients and caregivers will complete the additional assessments (memory skills and health literacy) as described in phase 2. Patients will also take an additional assessment of cognition levels, as described below.

The Blessed Orientation Memory Concentration (BOMC) assessment is a validated measure of cognitive function. This assessment will be conducted through verbal facilitation by a study team member, in which patients will be asked to repeat and recall information, replicating their memory and concentration skills [62]. The final score is based on a weighted calculation and assesses the likelihood of cognitive disability, with a higher score representative of a clinically meaningful cognitive impairment [63]. The BOMC assessment tool is an appropriate measure to evaluate the memory and concentration of users performing tasks in each prototype.

#### Phase 4: Final Evaluation of Usability, CWL, and Performance

##### Overview

Patients, caregivers, and health care workers will complete the preassessments as described in phase 3. Patients and caregivers will continue to participate in quantitative and qualitative assessments as described in phase 3, excluding the think-aloud sessions. In phase 4, patients and caregivers will also be asked to participate in task analysis and performance assessments of the DCE and BWS within the prototypes, including the evaluation of tasks using the Single Easy Questionnaire (SEQ), tracking time to complete, and the number of errors.

Health care workers will continue to participate as described in phase 3.

##### Quantitative Assessments: Usability

The DCE and BWS choice tasks within each prototype will be treated as a task. During phase 3, participants will evaluate the usability of the prototypes by completing the SEQ after each task within each prototype. The SEQ is an experimentally validated tool and demonstrated as reliable, valid, and sensitive [64]. The SEQ is based on a 7-point scale, assessing how difficult users found a task, with average scores reported to be between 5.3 and 5.6 [64]. This posttask questionnaire will allow us to compare parts of the interface or workflows that are perceived as most problematic. As participants will be completing a series of assessments, we have chosen the SEQ as it is minimally disruptive, and helps understand participants’ attitudes toward the interface without subsequent tasks interfering with the user’s memory of the task just completed [47].

##### Quantitative Assessments: Performance

Participants will perform simulated tasks within the prototype and their responses will be recorded via the screen capture video software included in iPad OS14. As patients and caregivers in phase 4 perform tasks, they will be observed by 2 human factors experts and screen capture (touchscreen strokes, eye movement, and pupillary dilation into the captured video for analysis of pupillary response) will be performed. Their performance will be recorded as the time to complete each prototype, as well as the number of errors encountered.

##### Participant Characteristics

Patients and caregivers will complete the additional assessments as described in phase 3.

### Data Analysis

#### Statistical Testing

The study is primarily descriptive, as we aim to capture the usability, CWL, and performance of participants using EHTs that include the DCE and BWS instruments.

Within-subjects testing will be conducted to compare preferences regarding the presentation of information, usability, CWL, and performance of the DCE and BWS within the prototypes. The order of presentation will be randomized for each participant to account for the effect of order and to ensure that information is not transferred across prototypes [65].

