#### DCE and BWS Choice Tasks

We used the established paper form of both the DCE and BWS to develop 2 medium-fidelity prototypes using Adobe XD version 40.0.22. All participants will access the prototypes through a study-provided iPad (8th generation). Each prototype is referred to as PRIME (*P*reference *R*eporting to *I*mprove *M*anagement and *E*xperience) but has distinct choice tasks as described below.

In the DCE, participants will go through a series of 10 hypothetical choice tasks, in which the same 5 attributes are presented (event-free survival, complete remission, time in hospital, short-term side effects, and long-term side effects) at different levels for each attribute within each task. For each choice task, participants will view differing profiles, consisting of attribute levels for “drug A” versus “drug B,” and will be asked to evaluate the benefits and risks for each, then select which drug they prefer, as depicted in Figure 2.

In the BWS, participants will go through a series of 10 choice tasks, in which the same 5 attributes are presented (event-free survival, complete remission, time in hospital, short-term side effects, and long-term side effects), but the levels of each attribute vary within each task. For each choice task, participants will view 5 outcomes and will be asked to choose 1 outcome that is the most important and 1 outcome that is the least important to them, as depicted in Figure 3.

To ensure the same number of choice tasks are displayed to users when measuring performance (time to complete) between the DCE and BWS, a tenth task was added to the BWS. The tenth task will repeat choice task 2 and will not be used in quantifying patient preferences. However, as choice task 2 and choice task 10 are identical, this will provide evidence regarding the consistency with which respondents select answers within the prototype.

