#### Phase 2: Evaluation With Healthy Volunteers

##### Overview

Healthy volunteers will be asked to complete a baseline questionnaire online via REDCap before the user testing session. Healthy volunteers will complete a short demographic questionnaire and will be asked to report on their race, ethnicity, education, household income, employment, and technology comfort level.

During the user testing session, healthy volunteers will be asked to compare and evaluate both the DCE and BWS prototypes as well as the visualizations within the Personalized Treatment Preferences Dashboard. Participants within this phase will be divided into 3 groups, each consisting of 5 users. Based on Nielson’s [43] user testing recommendations, user groups of 5 should be sufficient to resolve approximately 75% of usability issues.

Data gathered will be used to make iterative improvements to each prototype and then presented to subsequent groups for further evaluation.

Healthy volunteers will provide subjective and objective feedback about each prototype utilizing the following assessment methods.

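### Randomising prototype order spreads order and learning effects but cannot prevent transfer, and the named paired t test has no order term: reword, balance the order and add a period term

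*Protocol article*

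**What the plan says.** Under Statistical Testing the design is within-subject: "Within-subjects testing will be conducted to compare preferences regarding the presentation of information, usability, CWL, and performance of the DCE and BWS within the prototypes". On sequence, "The order of presentation will be randomized for each participant", and the stated purpose is "to account for the effect of order and to ensure that information is not transferred across prototypes". No blocking or balancing of order within a group is mentioned.

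Under Quantitative, the paired t "test will be utilized to evaluate the statistical significance of the PSSUQ, SEQ, NASA-TLX, and performance", applied "within the prototypes for each group in all relevant phases". Analysis of variance is named for comparisons across groups. Neither analysis is given an order or period term. P below .05 and 95% CIs are the declared criteria.

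Groups are small. For phase 2, "Participants within this phase will be divided into 3 groups, each consisting of 5 users". The phase 3 overview describes two groups, each of 10 patients and 10 caregivers. The section on the choice tasks describes each prototype as 10 tasks "in which the same 5 attributes are presented", and the attribute list is identical for the DCE and the BWS.

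**The concern.** This is a two-period crossover. The article credits randomised order with two results: dealing with order, and preventing transfer.

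The second cannot follow. Someone who has worked through 10 tasks on five attributes brings that familiarity to the second prototype, whichever it is. Randomisation decides who carries it in which direction; it does not remove it.

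The first is only half delivered. The allocation takes account of order, but the analysis named for it does not. Time to complete, errors, SEQ and NASA-TLX can all plausibly move with practice or fatigue, and patients are 60 or older and on active chemotherapy. At stake is the precision of the DCE-BWS contrast in groups of 10, and a reader's belief that carry-over has been excluded. That contrast is the study's primary objective.

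**Working it through.** The article gives no order effect, SD or power, so there is no figure of its own to reproduce. The effect sizes below are assumptions, shown as a range.

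**Model.** For participant i, the DCE-minus-BWS difference is d = δ + π·s + e. Here s = +1 if the DCE comes first and −1 if the BWS comes first, and e has SD 1. The position effect π is in SDs of the order-free paired difference. Group sizes of 5 and 10 are from the article. The test is two-sided at 0.05.

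**1. Order splits, if order is drawn independently for each participant.**
- n=5: 4:1 or worse has probability 2(5+1)/32 = 37.5%. Exact balance is impossible.
- n=10: 5:5 has probability 252/1024 = 24.6%. A split of 7:3 or worse has probability 2(120+45+10+1)/1024 = 34.4%.

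**2. Shift of the group mean, π(n₁−n₂)/n.**
- n=5: 0.2π at 3:2, 0.6π at 4:1, π at 5:0.
- n=10: 0 at 5:5, 0.2π at 6:4, 0.4π at 7:3.
- Averaged over the randomisation, the shift is zero at both sizes.

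**3. Error rate of the plain paired t test.** In simulation under simple randomisation with no true difference, type I error stayed at about 5%: 0.050 to 0.053 at n=5 and n=10 for π from 0 to 0.8, and at most 0.056 (n=5) at π = 1.0. Given the split it varies. At n=10 and π = 0.5 it is about 3% at 5:5, 6% at 7:3 and 10% at 8:2.

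**4. Width.** The SD of d is √(1+π²): 1.03, 1.12 and 1.41 for π = 0.25, 0.5 and 1.0. At n=10 the mean 95% CI half-width is 0.70 SD with no position effect and 0.78 SD at π = 0.5.

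**5. Balanced order plus a period term.** The SE is √[(1/n₁+1/n₂)/4] on n−2 df. At 5:5 this is √0.1 = 0.316 on 8 df, whatever π is. Power at δ = 0.8:

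| π | n=10 plain, simple randomisation | n=10 balanced, adjusted | n=5 plain, simple randomisation | n=5 balanced (3:2), adjusted |
|---|---|---|---|---|
| 0 | 62% | 60% | 28% | 24% |
| 0.25 | 59% | 60% | 27% | 24% |
| 0.5 | 52% | 60% | 23% | 24% |
| 0.8 | 41% | 60% | 18% | 24% |

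**6. Balancing alone is not enough.** With order forced to 5:5 but left out of the analysis, type I error at n=10 falls to 3.0% at π = 0.5 and 0.7% at π = 1.0. The test is then conservative, so the period term is needed as well.

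**The case against.** A reader might infer that order effects bias every small group's result, that the paired t test is invalid, or that its interval is too wide. The documents do not support this. With order randomised for each participant, a pure position effect averages to zero and type I error stays near 5%. The extra width is what keeps coverage right when order varies by chance. About a quarter of groups of 10 would be exactly balanced even without blocking.

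Other points on that side:
- The article does not say the order is unblocked. Block structure and model terms are often left to a full protocol or SAP, neither of which is shown, and the article promises a statistician's help. This stands, so the split probabilities are conditional on simple randomisation. It does not excuse the sentence on transfer, which is wrong as written.
- The study is declared primarily descriptive, and no power claim rests on these tests. This lowers the severity. It does not dispose of the point, because P values and CIs are still to be used to establish differences.
- A period term does not help groups of 5 unless the position effect exceeds about 0.5 SD, and it cannot be estimated in a 5:0 split (2/32 = 6.25% of such groups). Phase 2 recruitment ended in September 2021, so order can no longer be blocked there. Both stand.
- Neither blocking nor a period term removes unequal carry-over. This stands. A comparison of first prototypes only would be 5 against 5 between people, with roughly 14% to 35% power for the same 0.8 SD effect (assuming within-person correlation of 0.7 to 0), so it would settle little.

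**Conclusion.** The point holds in a limited form. The claim that randomised order prevents transfer is wrong on the face of the article and needs correcting. The absence of an order term in the named tests costs precision and leaves each group's estimate open to chance imbalance; it does not invalidate the test.

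The size of the loss depends on an unknown position effect: negligible at 0.25 SD, 8 percentage points of power at 0.5 SD and about 19 at 0.8 SD, for n=10 and a true difference of 0.8 SD. These figures assume simple randomisation, normal errors and equal carry-over in both orders. If carry-over were unequal, the contrast would be biased at any sample size, but nothing in the documents shows that it is. Severity is minor to moderate.

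**What to change.** 1. In Statistical Testing, replace the stated purpose of randomising order with a statement that it is done to balance order effects. Add that unequal carry-over between the two orders cannot be excluded.
2. For the remaining patient and caregiver groups, randomise order in balanced blocks: 5:5 within each 10 patients and 5:5 within each 10 caregivers. Phase 3 recruitment began in January 2022, so this can apply only to participants not yet allocated.
3. In Quantitative, analyse the DCE-BWS difference with a period (order) term, in both the within-group and the across-group analyses.
4. For the completed phase 2 groups of 5, use a period term only with the 15 volunteers pooled, not group by group. Because the prototypes were to be revised between groups, say so when reporting the pooled result.

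The cost is a blocked list and a few lines of text, with no extra participants. The statistical price is one degree of freedom: if there is no position effect, power at n=10 falls from about 62% to 60%.
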